# **Xience V stent vs. Cypher stent**

## **IN ALL MCL PCI PATIENTS A RANDOMIZED TRIAL**

**June 2007**

**Amendment 1**

**Amendment 1 to Appendixami study version of 24 april 2007.**

- **Referring to page 7 of protocol extra text:**

**"The APPENDIXAMI study will stop at the time the XAMI study stops. This includes an early stop reason as indicated by the DSMB".**

- **Referring to page 18 of protocol STUDY INSURANCE:**

**"Following the advice of the central Medical Ethical Committee of this study, the RTP0 of the MCL hospital, no additional insurance is needed. The patients are insured by the WA hospital insurance at Medirisk".**

## 1. STUDY SUMMARY

|                      |                                                                                                                                                                                                                                                                                                |
|----------------------|------------------------------------------------------------------------------------------------------------------------------------------------------------------------------------------------------------------------------------------------------------------------------------------------|
| Type of Study        | Single-centre, prospective, randomized (XienceV versus CYPHER)
XAMI APPENDIX                                                                                                                                                                                                                |
| Centres              | 1 centre                                                                                                                                                                                                                                                                                       |
| Number of subjects   | A number of 2000 patients, for each treatment arm 1000 patients                                                                                                                                                                                                                                |
| Purpose of the study | The purpose of this study is to assess the effectiveness of the Xience stent compared to the CYPHER stent in the PCI treatment of all patients in the MCL during 2007-2008. This study runs parallel with XAMI study                                                                    |
| Primary endpoint     | Clinical MACE at 1 year (cardiac mortality, non-fatal myocardial infarction, TVR)                                                                                                                                                                                                              |
| Secondary endpoints  | 

• (Sub)-acute stent thrombosis (SAT) at 30 days and late stent thrombosis (LST) at 1, 2 and 3 year.

• Clinical MACE at 30 days and 2 and 3 years (cardiac death, non-fatal MI, TVR).

• All cause mortality at 1, 2 and 3 year.

 |
| Study duration       | 18 months enrolment, and 36 month follow up                                                                                                                                                                                                                                                    |

### *Study design*

This is a prospective randomized single-centre registry study designed to assess the clinical performance of the Xience stent in **all MCL PCI patients** compared to CYPHER during 2007 and 2008.

The patients will undergo a clinical examination to assess their clinical status and the occurrence of adverse clinical events before and after the procedure and follow-up inquiry at 30 days, 1, 2 and 3 years after the procedure.

### ***Number of patients***

A total number of 2000 patients should be randomized between Xience and CYPHER and enrolled in the study.

### ***Study duration***

The duration of the enrolment period will terminate when a total number of 2000 patients will be enrolled.

The estimated study duration is 54 months, i.e. 18 months enrolment and 36 months follow up.

### ***Follow-up methods***

Patients will be submitted to clinical examination or assessment at every scheduled follow-up (30 days and 1, 2 and 3 year) by telephone and/or inquiry at referring cardiologist:

|                      | Pre-procedure | Post-procedure | At discharge | 1 month follow-up | 1,2,3 y follow-up |
|----------------------|---------------|----------------|--------------|-------------------|-------------------|
| Physical examination | X             | X              | X            |                   |                   |
| Adverse events       | X             | X              | X            | X                 | X                 |
| Coronary Angiography | X             | X              |              |                   |                   |
| Blood Sampling       | X             | X              |              |                   |                   |

### ***Data Reporting***

Data will be recorded on dedicated Case Report Forms.

## 2. INTRODUCTION AND STUDY RATIONALE

### *Rationale for use of DES in all comers and XAMI appendix*

In the Netherlands DES stents are implanted routinely in 3 centres in a high percentage of patients (Rotterdam x2, Leeuwarden). In the MCL from 2004 the Cypher stent is used routinely. The first clinical results of MCL are encouraging with a low mortality, a low rate of (late) stent thrombosis and re-intervention (rePCI). Results of MCL are competitive to those in the literature. However recent retrospective analyses and registries suggest a higher late risk for stent thrombosis in DES stent patients compared to bare metal stent patients (NEJM 2007). The FDA recently warned against off-label use of DES, which resulted in a drop of DES use by 30%. All this could be due to a shift towards a change in PCI indication (longer lesions, smaller vessels and total occlusions) and the use of DES stents. Randomized prospective data are lacking.

Based on the encouraging results of the MCL the current PCI strategy with DES is however continued, with the exemption that all patients are monitored closely and that follow up is extended. The present single-centre study is an outcome study of all patients treated in the MCL and is part of the XAMI study where there is a focus on AMI patients in a multi-centre setting.

Using randomization the clinical effects of the new generation XienceV stent can be assessed against the golden standard, Cypher stent in an unbiased fashion. Furthermore the data of Xience V stents can be pooled with those of other centres in the Netherlands.

### *Rationale for use of DES in AMI patients*

The benefit of primary Percutaneous Coronary Intervention (PCI) over thrombolytic therapy for acute ST-elevation myocardial infarction (STEMI) has been well established. Keeley et al. showed in a meta-analysis a clear benefit of PCI, including for patients transported from a non-interventional hospital to an intervention center for primary PCI.

Superiority of stenting versus balloon angioplasty in primary PCI was shown in several randomised trials. The benefit in Major Adverse Cardiac Events (MACE: death or reinfarction or Target Vessel Revascularisation (TVR)) in these trials was almost entirely due to reduction in TVR. At 1 year this reduction after stenting was sustained, even compared to patients in whom an optimal "stent-like" result was achieved with balloon angioplasty. No significant reduction in mortality or reinfarction was apparent.

Despite the reduction of TVR in bare metal stents compared to balloon angioplasty, restenosis rates are still significant. In the low risk randomised Stent-PAMI infarct study, 6 months angiographic restenosis rates were 20.3 % for the stented patients and at 1 year ischemic TVR was needed in 16.0 % of patients. In the more contemporary CADILLAC trial, ischemic TVR at 1 year was 13.3%. In these trials only low risk non-shock patients were included.

Suryapranata et al. recently reported the results of 1683 consecutive patients with STEMI (4 % of patients presenting with Killip class 3-4) treated with primary PCI. At 1 year, TVR was performed in 17.3% of patients after stenting and in 19.3 % of patients after balloon

angioplasty. In contrast to the studies reported above, the difference between balloon and stent was not significant in this randomised study. Bare stent thrombosis was seen in 4.8 % of stented patients at 1 year, of which 3.7 % between 0 and 30 days. At 1 year, MACE was 23.1 % in stented patients.

Despite the clear benefit of primary PCI over thrombolysis and the low mortality in several trials, the MACE rate at 1 year is substantial. Most of the MACE is caused by unplanned reinterventions in the infarct related vessel.

The efficacy of drug-eluting stents (DES) to treat coronary artery stenosis in stable patients has been proven in recent trials.

The use of DES in acute myocardial infarction could be an effective way to decrease the MACE rate after primary PCI. However, the potential risk of higher thrombogenicity has led to cautious use in acute coronary syndromes. Despite early FDA warnings no significant increase in stent thrombosis has been substantiated in stable patients so far, though this is depending on definition and method of data analysis. Premature discontinuation of double anti-platelet therapy is the strongest predictor of stent thrombosis.

The risk of stent thrombosis after DES in STEMI patients has not been studied in large randomised trials, but data from smaller registries and randomized trials has recently been published. Lemos et al. detected no angiographic stent thrombosis at 1 year follow-up in 186 consecutive STEMI patients treated with a sirolimus-eluting stent. Hofma et al. reported the results of 136 consecutive patients treated with Taxus stents for STEMI. 2.9 % subacute stent thrombosis was seen at 30 days and no additional stent thrombosis up to 1 year. In this total DES group (322 patients) incidence of stent thrombosis after 1 year was 1.2 %. This is not higher than rates reported for bare stents in stable patients and compares favourably to the rates reported by Suryapranata et al. for bare stents in STEMI. The STRATEGY trial, a single center primary PCI trial randomising patients to abciximab and bare metal stent or tirofiban and sirolimus-eluting stent showed no subacute stent thrombosis at 30 days in the sirolimus-eluting stent vs. 3 % in the bare stent group (not significant). In both groups no late thrombosis was seen up to 8 months.

The TYPHOON trial randomized 712 patients who underwent primary PCI for STEMI to sirolimus-eluting stent or bare metal stent. Very similar percentages of stent thrombosis of 3.4 % in the sirolimus group vs. 3.6 % in the bare stent group at 1 year were reported, using a liberal definition of stent thrombosis. The PASSION trial, randomizing 619 patients to a paclitaxel-eluting stent or the same uncoated stent in acute myocardial infarction reported similar stent thrombosis incidence in both groups of 1 % at 1 year, using a stricter definition.

While stent thrombosis risk does not seem to be higher with DES, a spectacular decrease in TVR was seen in the studies mentioned above. Lemos reported 1.1 % TVR at 1 year in 186 patients treated with sirolimus-eluting stents. Both patients were treated within 48 hours because of persistent complaints with stent edge dissection and incomplete lesion coverage. Thereafter no single patient returned for TVR up to 1 year. Total MACE at 1 year was 9.7 %. The STRATEGY trial reported 7 % TVR in the DES group versus 20 % in the bare stent group at 8 months follow-up. In the TYPHOON trial TVR was 5.6% in the sirolimus patients vs. 13.4 % in the bare stent group at 1 year, with target vessel failure (TVR or recurrent infarction or target-vessel related death) of 7.3 % vs 14.3 % in the control group. For the paclitaxel-coated stent, Hofma reported 6.6 % TVR, mainly caused by a few stent thrombosis patients, who had received complex bifurcation stenting. In this group MACE was 14.7 % at 1 year. In these all-comer groups more than 12 % of patients were in shock

and in 15 % of patients multiple vessels were treated at the index procedure. However, the primary endpoint of cardiac death, recurrent myocardial infarction or TLR at 1 year was not significantly less for the paclitaxel-coated stent compared to the uncoated stent in the PASSION trial (8.8% vs 12.8% p=0.09). It may be argued that the trend is clear but the study was underpowered to show a significant difference.

In conclusion, in early studies using DES for PCI in STEMI, stent thrombosis rates are reassuringly low, at least up to 1 year, and at least comparable with contemporary data with bare stents. It seems advisable to keep procedures simple and, if possible, to avoid bifurcation stenting in the acute setting. A spectacular drop in TVR was reported in the patients treated with DES, thereby reducing the MACE. Bare stents do not decrease mortality and re-infarction rate compared to balloon angioplasty. This is also not to be expected from DES. Despite the fact that larger randomised studies are needed to confirm the data, the use of DES for STEMI seems safe and very effective. However, long-term safety of DES for STEMI still has to be confirmed in trials with longer follow-up.

#### *Concerns about delayed healing after DES and thrombosis risk*

Despite the favourable clinical data of DES in large trials and in patients with acute myocardial infarction or acute coronary syndromes, delayed healing response is a matter of concern. Some increase in late stent thrombosis has been reported during the 2006 ESC and TCT meetings (presentations by E. Camenzind, P. Wenaweser, G. Stone) despite the fact that absolute numbers were depending on definition and analysis method of the raw patient data. Despite the fact that so far the data is not yet very alarming, the very high hazard ratio of stent thrombosis after premature discontinuation of clopidogrel is illustrative for the immature healing response after injury in the first months and maybe up to two years after DES implantation.

Delayed vessel wall healing also implies delayed endothelialization and impaired endothelial function post intervention. Recently, several reports have been published suggesting endothelial dysfunction at least up to 6 months after implantation of sirolimus-eluting stents.

Possible mechanisms of delayed healing include a hypersensitivity reaction to the non-erodable polymer on the surface of the stent from which local drug delivery is facilitated or a direct effect of the drug on the endothelial cells.

#### *Possible advantage of Xience V stent over other DES*

1. The Xience V stent has very thin stent struts (81 µm) compared to the Cypher stent (134 µm).

It has been shown before for bare metal stents, that strut geometry and thickness influence the vessel wall injury and neointimal proliferation. Less extensive vessel wall injury during stenting with thin strut stents may influence the time-table of wound healing response and restoration of endothelial function.

2. This thinner strut thickness and lower crossing profile of the Xience V stent compared to the Cypher stent increases the deliverability success of the stent, especially in tortuous and calcified lesions, as well as in distal lesions. Moreover, lower profile may decrease the risk

of polymer damage during delivery, as was recently shown with scanning microscopy for a Cypher stent of which delivery through another stent had failed.

3. The non-erodable two polymers used on the Xience V stent are acrylic and fluoro polymers, biocompatible and already used for years in vascular sutures. They may result in less inflammatory reaction after stent implantation. Less inflammatory response or shorter inflammatory response may also have a beneficial influence on vascular healing and neointimal proliferation.

4. In animal models, delayed arterial healing and poor re-endothelialization was demonstrated after oral everolimus in a rabbit model of iliac artery stent implantation. Despite the fact that low dose everolimus did not show these effects, the suppression of neointima was similar in the high and low dose group. This suggests a wide therapeutic window and the possibility to keep the detrimental effects on vascular wall healing limited together with effective suppression of neointimal proliferation. In fact, recently, Finn et al. demonstrated almost complete endothelialization of a Xience V stent with even tight intercellular junctions, 14 days after implantation in a porcine coronary artery. This was in contrast to poor endothelialization of the TAXUS stent in the same model.

The issues raised above provide the rationale for testing the performance of the Xience V stent in patients with acute myocardial infarction and in all comers.

In this protocol of the **XAMI APPENDIX** study the Xience V stent will be tested against the gold standard of drug-eluting stents at this moment, the Cypher (sirolimus-eluting) stent. This study runs parallel with XAMI study.

The APPENDIXAMI study will stop at the time the XAMI study stops. This includes an early stop reason as indicated by the DSMB.

## 4.2 CYPHER DES

The Cypher stent (Cordis Co, Warren, NJ, USA) is a 316 L stainless steel metal stent with a polymer coating eluting the anti-proliferative drug sirolimus. The strut thickness of the BX-Velocity stent, the platform of the Cypher stent is 134  $\mu\text{m}$  (0.0055 inch).

For use of the device please consult the instructions for use.

## 5. STUDY DESIGN

This is a prospective randomized study designed to compare the effectiveness and safety, defined as clinical MACE at 12 months follow up, of the Xience Stent with the CYPHER stent in all patients treated for PCI in MCL. In order to study the long-term safety of the both DES, follow-up is extended to 3 years.

### 5.1.1 Endpoint of the Study

The **primary endpoint** of the study is to assess the 12 month MACE (cardiac death, non-fatal MI, TVR) in all MCL PCI patients comparing the Xience stent to the CYPHER stent.

The **secondary endpoints** are:

- (Sub)-acute stent thrombosis (SAT) at 30 days and late stent thrombosis (LST) at 1, 2 and 3 year. (Definite and Probable, according to ARC definition). Possible stent thrombosis will be reported separately.
- Clinical MACE at 30 days and 2 and 3 years (cardiac death, non-fatal MI, TVR).
- All cause mortality at 1,2 and 3 year.
- Inability to deliver Cypher or Xience stent (cross over)

### 5.1.2 Definitions

Stent thrombosis:

According to the recently proposed ARC (Academic Research Consortium) definitions (Cutlip et al. TCT 2006).

- **Definite:** When confirmed by angiography (angiographic documentation of target vessel occlusion or visual thrombus) or when pathologic confirmation of acute thrombosis in ACS patient is made.
- **Probable:** any unexplained death within 30 days or target vessel MI without angiographic confirmation of thrombosis or other identified culprit lesion.
- **Possible:** any unexplained death after 30 days.
- **Timing:**

|            |                    |
|------------|--------------------|
| Early:     | Acute < 24 hours   |
|            | Subacute 1-30 days |
| Late:      | 30 days – 1 year   |
| Very Late: | > 1 year           |

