#### Target lesion revascularization (TLR):

- TLR is defined as any repeat percutaneous intervention or by-pass grafting of the target lesion previously treated successfully with the stent or the 5 mm proximal or distal to this initial lesion.

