## **9. FOLLOW-UP**

After discharge, patient follow-up will be performed after 30 days and 1,2,3 year by questionnaires. Repeat angiography will only be performed clinically driven by symptoms or signs of ischemia or when deemed necessary by the cardiologist. Information about in-hospital outcomes will be obtained from our institutional electronic clinical database and by review of the hospital records for those discharged to referring hospitals. Post-discharge survival status will be obtained from the Municipal Civil Registries at 1 month and 1, 2, 3 year. All repeat interventions (surgical and percutaneous) and re-hospitalizations will prospectively be collected during follow-up. Questionnaires regarding anginal status, intercurrent events and medication use will be discussed with all living patients by telephone at 12 months. Referring physicians and institutions will be contacted for additional information if required.

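### The written criterion for definite stent thrombosis requires no location in or next to the study stent and, on angiography, no acute presentation, so other occlusions of the target vessel can be counted.

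*Protocol*

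**What the plan says.** Protocol section 5.1.2 opens the entry on stent thrombosis with a reference: "According to the recently proposed ARC (Academic Research Consortium) definitions". It then writes out its own criteria. An event is definite on one of two routes. The angiographic route is "angiographic documentation of target vessel occlusion or visual thrombus". The pathology route applies "when pathologic confirmation of acute thrombosis in ACS patient is made". The probable category takes in early unexplained deaths, and target vessel infarctions for which angiography has shown neither thrombosis nor a different culprit.

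Further down the same section, target lesion revascularization is confined to "the target lesion previously treated successfully with the stent or the 5 mm proximal or distal to this initial lesion". Target vessel revascularization is defined for the whole vessel.

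Section 5.1.1 lists stent thrombosis first among the secondary endpoints, at 30 days and 1, 2 and 3 years, with definite and probable events together and possible events reported separately. It repeats the ARC reference. Section 5 describes the main comparison as one of "effectiveness and safety, defined as clinical MACE at 12 months follow up". Section 9 says of later imaging: "Repeat angiography will only be performed clinically driven by symptoms or signs of ischemia or when deemed necessary by the cardiologist".

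**The concern.** The angiographic route asks for an occluded target vessel or a visible thrombus and leaves open where in the vessel it lies and how the patient presented. Two kinds of event that are not stent thrombosis satisfy the words as written: a stent that has closed slowly through restenosis, and an occlusion in an unstented part of the same artery.

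The endpoint matters to this trial. Section 2 gives a possible late risk of stent thrombosis as background to closer monitoring and longer follow-up, and section 5 extends follow-up to three years for long-term safety. Section 2 also says that reported thrombosis rates depend on the definition used. With few events expected, a handful of misclassified ones can change the comparison. If such events are unrelated to stent type, they dilute a real relative difference. If restenosis differs between the stents, part of that difference could be reported as a thrombosis difference.

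**Working it through.** **Comparison of the protocol's own criteria**

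| Criterion | Location required | Acute presentation required | Other culprit excluded |
|---|---|---|---|
| Definite, angiographic route (5.1.2) | target vessel only | no | no |
| Definite, pathology route (5.1.2) | none written | yes: acute thrombosis in an ACS patient | no |
| Probable, infarction route (5.1.2) | target vessel | yes, in that an infarction is required | yes |
| Target lesion revascularization (5.1.2) | treated lesion plus 5 mm either side | not applicable | not applicable |

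Three things follow.

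1. The two routes to definite differ. Pathology needs an acute thrombosis in an acute coronary syndrome; angiography needs neither.
2. The order of certainty is broken. Take an infarction caused by an occlusion in an unstented segment of the target vessel. The identified other culprit keeps it out of probable, yet the occlusion satisfies the words of definite, the more certain category.
3. The authors had a location rule available and used it for target lesion revascularization, but not here.

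**Can such events be observed?** The follow-up table in section 1 schedules angiography only before and after the procedure. Section 9 then allows it for ischaemia or at the cardiologist's discretion. Ischaemia-driven angiography can itself show a restenotic or remote occlusion, and discretion leaves some room for incidental ones. How often this would happen is not stated.

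**Size.** The protocol has no figure to reproduce: section 5.2.1 says that no sample size calculation was done. The following shows direction only.

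Let p1 and p2 be the true control and test rates, and x the share of patients in each arm with a wrongly counted event, equal in both arms and not overlapping with true events. The observed risk ratio is (p2 + x)/(p1 + x), and the false share in the control arm is x/(p1 + x). Power uses n = 1000 per arm (section 1) and an assumed two-sided 5% level:

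Φ{ [|p1 − p2| − 1.96·√(2p̄(1 − p̄)/n)] / √([P1(1 − P1) + P2(1 − P2)]/n) }, with P1 = p1 + x, P2 = p2 + x and p̄ their mean.

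The 3.4% is a one-year sirolimus rate quoted in section 2 from a STEMI trial that used a liberal definition. All other rates, and every x, are assumptions.

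| p1 vs p2 | x | Observed risk ratio | False share, control | Power |
|---|---|---|---|---|
| 3.4% vs 1.7% | 0 | 1.7/3.4 = 0.50 | 0% | 67% |
| | 0.5% | 2.2/3.9 = 0.56 | 13% | 60% |
| | 1.0% | 2.7/4.4 = 0.61 | 23% | 54% |
| | 2.0% | 3.7/5.4 = 0.69 | 37% | 45% |
| 2.0% vs 1.0% | 0 | 1.0/2.0 = 0.50 | 0% | 45% |
| | 0.5% | 1.5/2.5 = 0.60 | 20% | 36% |
| | 1.0% | 2.0/3.0 = 0.67 | 33% | 30% |
| | 2.0% | 3.0/4.0 = 0.75 | 50% | 23% |

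The absolute difference is unchanged, since (p1 + x) − (p2 + x) = p1 − p2, but it is estimated less precisely. The risk ratio moves towards 1.

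**The case against.** The strongest reply is that the entry must be read whole. It is headed as stent thrombosis, the bracket explains how that diagnosis is confirmed by angiography, the vessel is the one that received the stent, and the ARC definitions are cited both here and in section 5.1.1. A reader might infer from the bracket alone that the criterion has no link to the stent, or that any visible thrombus qualifies. The documents do not support that: the heading, the confirmation wording, the citation and the limit to the target vessel give a link, though a loose one. What they do not give is a required location or presentation. The cited text is not reproduced, and nothing says that it prevails where the written criteria differ. Whether it would close the gap cannot be checked from the protocol, and the point does not rest on it.

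A reader might also take stent thrombosis to be the trial's key safety endpoint. The protocol does not call it that. Section 5 defines safety through 12-month MACE, of which stent thrombosis is not a component.

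The contrast with target lesion revascularization is only partly telling: that event is not a listed endpoint, and target vessel revascularization, which is part of the primary endpoint, is deliberately vessel-wide. It shows that a location rule was at hand, no more.

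Finally, it is tempting to quantify the problem from the 1.2% one-year rate in section 2. That figure pools 322 STEMI patients. The 2.9% of 136 paclitaxel patients is about 4 events, the 186 sirolimus patients had none, and 4/322 = 1.2%. It is therefore no estimate for a sirolimus control arm in all comers. This objection stands in full.

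**Conclusion.** The point holds as a defect of wording with a possible, unquantified effect. As written, the angiographic criterion can admit restenotic occlusions and occlusions elsewhere in the target vessel as definite stent thrombosis. It can do so; the documents do not show that it will, or how often. The first-listed secondary endpoint is exposed; the primary endpoint is not.

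No magnitude can be derived from the documents. The tabulated risk ratios rest on assumed rates and on equal misclassification in both arms, and they support only the direction: towards no difference on the ratio scale. If misclassification depended on stent type, the direction would not be known. Because the endpoint combines definite with probable events, the false share among all counted events would be smaller than the share among definite events alone. Correction is worth making because it is cheap and the protocol itself treats the definition as consequential.

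**What to change.** In section 5.1.2, require for the angiographic route that the thrombus or thrombotic occlusion lies in or adjacent to the study stent, with an acute ischaemic presentation. A margin like the "or the 5 mm proximal or distal to this initial lesion" used for target lesion revascularization would serve, but the reference point must be stated. That margin runs from the lesion, and section 7.4 has the stent extend 2.5 mm beyond the lesion on each side, so 5 mm from the lesion is 5 − 2.5 = 2.5 mm from the stent edge.

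Alternatively, state that the full cited definition governs wherever the protocol's wording differs.

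In either case, report other target vessel occlusions separately and record the location of the finding on the event form. Leave the probable category unchanged: its infarction route already excludes events with another identified culprit, and without angiographic confirmation there may be no segment to locate.

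The cost is one sentence, one form field and slightly fewer counted events. Treatment, visits and sample size do not change.

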### **5.2.3 Enrolment criteria**

#### Inclusion criteria

- 1) Patient is willing to sign the informed consent
- 2) Patient is willing to perform all follow-up examinations as required by the protocol
- 3) Patient eligible for coronary revascularization intervention by PCI and stenting
- 4) Patient is located in a geographic area that will enable contact by the study site for follow-up.

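### Section 5.1.2 accepts pathology as proof of definite stent thrombosis only in an undefined ACS patient, so some proven fatal cases fit no category in this all-comers trial

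*Protocol*

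**What the plan says.** The protocol's section 5.1.2 (Definitions) sets out three grades of stent thrombosis, introduced as "According to the recently proposed ARC (Academic Research Consortium) definitions".

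- **Definite** has two limbs. The angiographic limb reads "When confirmed by angiography (angiographic documentation of target vessel occlusion or visual thrombus" and carries no restriction on the type of patient. The pathology limb reads "or when pathologic confirmation of acute thrombosis in ACS patient is made".
- **Probable** is "any unexplained death within 30 days or target vessel MI without angiographic confirmation of thrombosis or other identified culprit lesion".
- **Possible** is "any unexplained death after 30 days".

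Section 5.1.1 makes stent thrombosis a secondary endpoint at 30 days and at 1, 2 and 3 years, and specifies which grades count: "Definite and Probable, according to ARC definition). Possible stent thrombosis will be reported separately".

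The population is not limited to ACS. Section 5 describes a comparison "in all patients treated for PCI in MCL", and the clinical entry criterion in section 5.2.3 is "Patient eligible for coronary revascularization intervention by PCI and stenting". The protocol does not say whether the ACS qualifier refers to the indication for the index procedure or to the patient's state at the event.

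**The concern.** The pathology limb is narrower than the trial population. Because the death limbs of probable and possible both require an unexplained death, a post-mortem finding of acute stent thrombosis closes those two routes. For a patient outside the ACS qualifier it does not open the definite route in exchange. Better evidence can then leave a death unclassified when the same death, not investigated, would have been classified.

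Stent thrombosis is a named safety endpoint. Section 2 gives late thrombosis as a reason for close monitoring, and section 5 extends follow-up to 3 years for long-term safety. Events are few, so the handling of one or two proven fatal cases is visible in the count. An undefined qualifier also allows two adjudicators to classify the same death differently.

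**Working it through.** The protocol states no figure on this point, so there is none to reproduce. The check is a classification by the rules of section 5.1.2, followed by a rough size.

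**Step 1: classification.** Take a patient without ACS at the index procedure who dies with autopsy-proven acute thrombosis of the study stent. Read the qualifier as the index presentation. Cross three yes/no factors (angiographic confirmation, target vessel MI, death up to or after day 30), which gives 2 × 2 × 2 = 8 cells.

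| Angiographic confirmation | Target vessel MI | Time | Category with autopsy |
|---|---|---|---|
| Yes | Yes or no | Either (4 cells) | Definite |
| No | Yes | Either (2 cells) | Probable |
| No | No | Up to day 30 | None |
| No | No | After day 30 | None |

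The proven case is lost in 2 of 8 cells. The cells are not equally likely, so 2/8 is not a rate.

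**Step 2: the same two cells without autopsy.** If nothing else explains the death, it is probable up to day 30 and possible afterwards. Up to day 30 the autopsy therefore removes the death from the counted endpoint. After day 30 the death without autopsy is only possible, which is not counted either. There the fault is that the proven case never enters definite and also leaves the possible group.

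**Step 3: the other reading.** If the qualifier means the patient's state at the event, a thrombosis that presents as ACS is definite whatever the index indication. The gap shrinks to deaths with no recognised ACS, such as unwitnessed sudden death.

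**Step 4: can the open routes be used?** Under section 9, repeat angiography is done only when clinically indicated, so a sudden death outside hospital would often have none. The re-infarction definition in section 5.1.2 needs a rise in CK and is timed from an index infarction. A sudden death may have no enzyme result, and a stable patient may have no index infarction.

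**Step 5: size.** The protocol gives no rates. All inputs except the 2000 patients are assumptions:

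- stent thrombosis over 3 years: 1% to 3%
- fatal: 20% to 40%
- fatal cases with pathology and no angiogram: 10% to 25%
- patients without ACS: 40% to 60%

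Events affected = 2000 × thrombosis rate × fatal × pathology only × non-ACS.

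- Low: 2000 × 0.01 × 0.20 × 0.10 × 0.40 = 0.16
- Midpoints: 2000 × 0.02 × 0.30 × 0.175 × 0.50 = 1.05
- High: 2000 × 0.03 × 0.40 × 0.25 × 0.60 = 3.6

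As a share of all stent thromboses, the range is 0.20 × 0.10 × 0.40 = 0.8% to 0.40 × 0.25 × 0.60 = 6.0%. Cases that the target vessel MI limb would catch, or that the event-time reading would make definite, are not subtracted. Each figure is therefore a ceiling for its own inputs.

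**The case against.** A reader might infer that any autopsy-proven thrombosis in a patient without ACS is lost from every category. The protocol does not support that. The angiographic limb of definite and the target vessel MI limb of probable have no ACS restriction, and the MI limb has neither a time limit nor a requirement that the event be unexplained. This objection stands and limits the point to the two cells above, although step 4 shows why those routes may fail in a sudden death.

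A reader might also infer that counting a fatal case depends on the entry diagnosis. That follows only on the index reading. The qualifier sits in a definition of the event and can equally describe the patient at that time. One could go further and hold that a fatal acute coronary thrombosis is itself an ACS, which would close the gap. The protocol says neither, so what remains is an undefined term that permits the gap.

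The bullets may be only a short paraphrase of the ARC definitions, which both sections invoke. Whether the ARC text closes the gap or contains the same qualifier cannot be judged from the protocol. The bullets are nevertheless the working rule that it prints.

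Finally, the consequences are small. A cardiac death counts in MACE, and any death in all-cause mortality, whatever its stent-thrombosis category. The rule is the same in both arms, and nothing in the protocol suggests that autopsy or ACS status differs by arm. All of this stands, and it sets the severity.

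**Conclusion.** The point holds in a narrow form, as a minor correction to a secondary safety endpoint. The rule as written leaves a pathology-proven stent-thrombosis death unclassified when three conditions meet: the patient is outside the undefined ACS qualifier, there is no angiographic confirmation, and there is no qualifying target vessel MI. Loss from the counted endpoint through having an autopsy is confined to deaths up to day 30. Later deaths are wrongly absent from definite and disappear from possible.

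The size, about 1 event and at most 3 to 4 in 2000 patients, rests entirely on assumed rates and only shows that the effect is small. The classification gap itself needs no assumed rate, only a literal reading of section 5.1.2. The primary endpoint is not affected, and no bias between the stents is shown.

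**What to change.** In section 5.1.2, delete the words *in ACS patient* from the pathology limb of definite. Suggested wording: *or when acute thrombosis of the study stent is confirmed by pathology, whatever the patient's indication or presentation*. All eight cells in the table then become definite, and the choice between the two readings no longer matters. Check the revised wording against the ARC definition cited in sections 5.1.1 and 5.1.2 before adopting it.

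The cost is a few words, with no new data or procedure. The reported stent-thrombosis rate may become very slightly higher.
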